#### Substudy 1: in-person MSK assessment

Participants will be assessed at either their home or their local ICU follow-up clinic. Participants will undergo a three part MSK assessment. First participants will be asked to record their current pain severity and location using a visual analogue scale (VAS) and body map, prior to being asked the Fear-Avoidance Belief Questionnaire (FABQ)^23^ and Douleur Neuropathique 4 Questions questionnaire.^24^ Second, participants’ upper and lower limb range of movement (ROM) will be assessed. Finally, participant strength will be assessed using the Medical Research Council Sum Score (MRCSS)^25^ and hand held dynamometry.^26^

#### Substudy 2: in-person functional assessment

Participants will be assessed in The Movement Science Laboratory at Oxford Brookes University. Participants will answer a series of questions regarding their physical health before undergoing the same MSK assessment as substudy 1. Participants will then undergo a series of physical assessments. Cross-sectional area of rectus femoris^27^ and biceps brachii^28^ will be measured using ultrasound (US) prior to isokinetic dynamometry (IKD) measurement of elbow flexion and knee extension.^29^ Participants will undertake a six minute walk test (6MWT)^30^ prior to being asked the Life-Space^31^ and QuickDASH (QD)^13^ questionnaires. Finally participants will be provided with an accelerometer,^32^ which they will be asked to wear for one week.

### Participant retention plan

The largest threat to validity in a prospective ICU follow-up study is selection bias through a high loss to follow-up rate, which is a common criticism of these studies.^33^ To counter this, the MSK-ICU study has a participant retention plan based on those used in previous successful studies.^34^ The primary study will follow-up participants at a single time point using a telephone questionnaire. There will be a clear method for the recording of both participant contact information and follow-up. A participant contact retention point will be factored into the ICU follow-up clinic at each centre, which occurs at two to three months post ICU discharge.

### Sample size

#### Primary study: telephone follow-up

The sample size calculation is based on the analysis requiring the largest sample size, which is to identify prognostic factors for the development of a lower MSK-HQ Score at six months after admission to ICU. Based on a local case mix data for the participating ICUs, approximately 1700 admitted patients have an ICU length of stay greater than 48 hours and are discharged to a ward within the hospital annually. Approximately 400 patients would be ineligible for participation in the study, and when accounting for an inpatient mortality of 7%, approximately 1200 eligible patients would be expected to survive to discharge from hospital. For the purpose of developing a prediction model, the MSK-HQ Score will be treated as a continuous variable. There are 15 potential baseline prognostic factors identified. Based on this number of predictors and assuming an approximately normal distribution of residuals, the minimum sample size required to estimate a multiplicative margin of error of 0.1 would be 249 individuals.^35^ Allowing for a 25% loss to follow-up, it is necessary to recruit 332 participants. This sample size and number of predictors would also ensure the estimation of a shrinkage factor ≥0.9 and a difference between apparent and adjusted *R*^2^≤0.02, even with a moderate anticipated *R*^2^ of 0.6.

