### Study procedures

#### Primary study: telephone follow-up

The primary study will involve a single telephone follow-up at six months following admission to ICU. Baseline data collected for all enrolled participants will include: demographics (age, ethnicity, sex, body mass index); admission information (reason for admission, severity of illness, ICU and hospital length of stay); ICU interventions (invasive ventilation and duration, neuromuscular blocking agents, steroids, prone positioning, mobilisation activity); and preadmission function and comorbidities (Functional Comorbidity Index,^16^ Clinical Frailty Scale 17 and MSK history).

Prior to the six-month telephone call, patients’ electronic health record will be checked for their current health status and location that is, in hospital, at home or died. At the start of the phone call, participants will be asked if it is a convenient time to talk and that the questionnaires will take approximately 20 min. If it is not a convenient time, the researcher will arrange to call the participant back at their best convenience. Participants will then be asked five questionnaires in the following order: Musculoskeletal Health Questionnaire (MSK-HQ),^18^ European Quality of Life Five Dimensions (EQ-5D-5L),^19^ employment questionnaire,^3^ Hospital Anxiety and Depression Score (HADS)^20^ and Impact of Events Scale-Revised (IES-R).^21^ The EQ-5D-5L, HADS and IES-R form the core outcome set recommended for ICU follow-up studies.^22^

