### Statistical analysis

#### Primary study: telephone follow-up

Descriptive statistics will be used to examine baseline characteristics and the distribution of individual components will be examined in the population. Descriptive statistics will also be used to examine the results of the questionnaires collected (point estimates and variability), including: MSK-HQ, EQ-5D-5L utility score, employment, HADS and IES-R. Correlation statistics will be used to assess the relationships between MSK-HQ and employment, EQ-5D-5L, HADS and IES-R. Multivariable regression will be used to assess for association of the baseline variables collected with the MSK-HQ score. A detailed statistical analysis plan describing all steps for the model development will be written and made publicly available.

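### The sample size budgets 15 model parameters, but the listed baseline data hold 16–17 single variables, and the stated R² difference of at most 0.02 is not met on the 249 analysed

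*Protocol article*

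**What the plan says.** All places are in the protocol article, under the primary study (telephone follow-up).

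- **Sample size.** The predictor count is given as "There are 15 potential baseline prognostic factors identified". From it follow "the minimum sample size required to estimate a multiplicative margin of error of 0.1 would be 249 individuals" and "Allowing for a 25% loss to follow-up, it is necessary to recruit 332 participants". The section adds "This sample size and number of predictors would also ensure the estimation of a shrinkage factor ≥0.9" and an apparent-minus-adjusted R² difference of at most 0.02, "even with a moderate anticipated" R² of 0.6.
- **Study procedures.** The first two groups of baseline data are given as "demographics (age, ethnicity, sex, body mass index); admission information (reason for admission, severity of illness, ICU and hospital length of stay". A third group, covering what was done during the ICU stay, reads "ICU interventions (invasive ventilation and duration, neuromuscular blocking agents, steroids, prone positioning, mobilisation activity". The last group has three pre-admission items: the Functional Comorbidity Index, the Clinical Frailty Scale and MSK history.
- **Statistical analysis.** "Multivariable regression will be used to assess for association of the baseline variables collected with the MSK-HQ score". The model-building steps are left to an SAP, which is announced but not shown.
- **Abstract.** The planned sample size is 334, not 332.

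**The concern.** The criteria behind these figures depend on the number of parameters in the fitted model, not on the number of phrases in a list. If the regression takes the collected baseline variables as they stand, it spends more degrees of freedom than the calculation allowed.

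At stake are the recruitment number and the two statements about overfitting. The second matters more: a results paper could repeat an assurance on R² optimism that the fitted model does not have.

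**Working it through.** **1. Count the predictors.** Taken as comma-separated items, the list gives demographics 4, admission 3, ICU interventions 5 and pre-admission 3: 4 + 3 + 5 + 3 = 15. This is probably where the 15 comes from. ICU stay and hospital stay are two variables, which gives 16. Splitting ventilation from its duration gives 17. A factor with k levels takes k − 1 parameters, so coding ethnicity or reason for admission with more than two levels adds to this. The article states no coding.

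**2. Reproduce the plan's figure.** The residual-SD criterion asks for the smallest n with max{√(χ²₀.₉₇₅/df), √(df/χ²₀.₀₂₅)} ≤ 1.1, where df = n − p − 1. A 95% interval is assumed, because the article gives no level. The criterion needs df = 233, so n = 234 + p. At p = 15, n = 249, and 249/0.75 = 332. Both stated figures reproduce exactly, which confirms that 15 was used as the parameter count.

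**3. Repeat for other counts.**

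| p | Analysed (234 + p) | Recruited (÷ 0.75, rounded up) | Margin factor at n = 249 |
|---|---|---|---|
| 15 | 249 | 332 | 1.0998 |
| 16 | 250 | 334 | 1.1001 |
| 17 | 251 | 335 | 1.1003 |
| 20 (assumed coding) | 254 | 339 | 1.1010 |
| 25 (assumed coding) | 259 | 346 | 1.1023 |

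**4. Shrinkage.** S = 1 + (p − 2)/[n ln(1 − R²app)], with R²app = [R²adj(n − p − 1) + p]/(n − 1). At n = 249, p = 15 and R²adj = 0.6, R²app = (0.6 × 233 + 15)/248 = 0.624 and S = 0.947. For p = 16, 17 and 25, S is 0.943, 0.939 and 0.910. It stays at or above 0.9 up to p = 27.

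**5. R² difference.** Apparent minus adjusted R² = p(1 − R²adj)/(n − 1), with R²adj = 0.6.

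| p | n = 249 | n = 332 | Analysed n needed for ≤ 0.02 |
|---|---|---|---|
| 15 | 6.0/248 = 0.0242 | 6.0/331 = 0.0181 | 1 + 6.0/0.02 = 301 |
| 16 | 6.4/248 = 0.0258 | 6.4/331 = 0.0193 | 321 |
| 17 | 6.8/248 = 0.0274 | 6.8/331 = 0.0205 | 341 |

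The limit is missed at 249 for every p from 15 upwards. It is met at 332 only for p of 16 or fewer. After 25% loss, 301, 321 and 341 analysed would mean recruiting 402, 428 and 455.

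If the 0.6 is read as the apparent R² instead, the differences at 249 are 0.0258, 0.0276 and 0.0294. At 332 they are 0.0190, 0.0203 and 0.0217, so only p = 15 passes there.

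**The case against.** The strongest defence has four parts.

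- **The list has 15 items as written.** This is true, so a flat statement that the article miscounts would be unfair. But a length of stay in ICU and one in hospital cannot enter a regression as one term unless they are combined, and nothing says that they will be.
- **The analysis sentence does not say that every recorded field enters, and coding belongs in the SAP.** This also stands in part. Candidate selection and coding may be settled there, and their absence from the article is not a fault. What remains is that the sample size premise and the analysis sentence, as printed, do not describe the same model.
- **The effect on size is trivial.** This stands. Each added parameter costs one analysed participant, and the margin at 249 is unchanged to two decimals for 16 or 17 parameters.
- **The R² limit fails for another reason.** This stands for 249, where 15 parameters already give 0.024. The predictor count decides the matter only on the more generous reading, in which all 332 recruits are analysed: 16 pass and 17 do not.

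A reader might infer that the sample size is seriously too small, or that none of the overfitting limits applies. The article does not support that. The larger shifts, such as 259 analysed at p = 25, rest on an assumed coding that appears nowhere in it, and the shrinkage limit holds even there.

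**Conclusion.** The point holds in a limited form. The 15 is a count of listed items used as a count of parameters, and entering the collected variables separately takes at least 16, even with one term per factor. The consequence for size is 1–2 more analysed and 2–3 more recruited. The shrinkage statement survives.

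The statement that does not survive is the R² difference of at most 0.02. On the number the calculation expects to analyse, it is about 0.024–0.027 for 15–17 parameters.

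This rests on the protocol's own R² of 0.6, taken as the adjusted value, and on its 25% loss. A lower R² would widen the gap: at 0.5 with 15 parameters, 15 × 0.5/248 = 0.030.

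The abstract's 334 equals the 16-parameter answer. It is tempting to conclude that an alternative count was once used, but that is only an inference. The documents show just that 332 and 334 disagree.

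**What to change.** 1. List the candidate predictors and state the number of parameters after coding, before outcome data are examined. Make the analysis sentence refer to that list instead of the baseline variables collected.
2. Restate the analysed and recruited numbers for that count (234 + p, then divided by 0.75), and reconcile 332 with the abstract's 334.
3. Replace the claim of at most 0.02 with the expected difference on the analysed number: about 0.024–0.027 for 15–17 parameters at R² = 0.6. Keep the shrinkage statement, checked for the final count.

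The cost is wording in the protocol and SAP, with at most a few extra recruits if the count is 16 or 17. Collapsing categories or dropping variables to hold the count at 15 is optional. It gives up information and does not repair the R² claim at 249. Keeping the 0.02 limit as a design target would instead need 301–341 analysed, a much larger change.

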**Methods and analysis:**

The MSK-ICU study is a multicentre prospective longitudinal cohort study, evaluating the MSK health state of ICU survivors 6 months after admission to ICU. The study consists of a primary study and two substudies. The primary study will be a telephone follow-up of adults admitted to ICU for more than 48 hours, collecting data on MSK health state, quality of life, employment, anxiety and depression and symptoms of post-traumatic stress disorder. The planned sample size is 334 participants. Multivariable regression will be used to identify prognostic factors for a worse MSK health state, as measured by the MSK-Health Questionnaire. In substudy 1, participants who self-report any MSK problem will undergo a detailed, in-person MSK physical assessment of pain, peripheral joint range of movement and strength. In substudy 2, participants reporting a severe MSK problem will undergo a detailed physical assessment of mobility, function and muscle architecture.

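### The stated bound of 0.02 on the apparent-versus-adjusted R² difference holds at 332 analysed but not at the 249 expected after the planned 25% loss, where the difference is 0.024 to 0.026: a minor correction to one sentence

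*Protocol article*

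**What the plan says.** All the relevant statements are in the protocol article, under Sample size, Primary study: telephone follow-up.

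- The outcome and model: "the MSK-HQ Score will be treated as a continuous variable".
- The number of predictors: "There are 15 potential baseline prognostic factors identified".
- The criterion that sets the number: "the minimum sample size required to estimate a multiplicative margin of error of 0.1 would be 249 individuals".
- The inflation for loss: "Allowing for a 25% loss to follow-up, it is necessary to recruit 332 participants".
- Two further properties are then claimed. The first is "This sample size and number of predictors would also ensure the estimation of a shrinkage factor ≥0.9". The second is "a difference between apparent and adjusted *R*^2^≤0.02". Both are qualified by "even with a moderate anticipated *R*^2^ of 0.6".

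The text does not say whether the last sentence refers to the 249 or the 332, or whether the R² of 0.6 is the adjusted or the apparent value.

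**The concern.** The difference between apparent and adjusted R² depends on the number of participants in the fitted model. A participant contributes to that model only with an MSK-HQ score from the single six-month telephone call, and the plan itself expects a quarter of recruits not to provide one. A property of the fitted model should therefore be stated for 249, as the residual-precision criterion in the same paragraph is. The claim about the R² difference comes directly after the recruitment figure and appears to have been met only there.

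At stake is the accuracy of a stated assurance. The sentence tells the reader that optimism in R² is held to a given tolerance at the planned size. If it is not, a reader comparing the eventual model with that tolerance is using a figure the design was not expected to deliver.

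**Working it through.** **Inputs.** From the sample size section: P = 15 predictors, taken as one parameter each; R² = 0.6; 249 analysed; 25% loss; 332 recruited. The confidence level for the margin of error is not given, so 95% two-sided is assumed. R² = 0.6 is tried both as adjusted and as apparent.

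**Step 1: reproduce the plan's own figures.** For a linear model with d = n − P − 1 residual degrees of freedom, the multiplicative margin for the residual SD is √max(χ²₀.₉₇₅,d / d, d / χ²₀.₀₂₅,d).

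- n = 248: 1.1001. n = 249: 1.0998. The smallest n with a margin of at most 1.1 is 249, as stated. This also confirms that the plan counts 15 parameters.
- 249/(1 − 0.25) = 332, as stated.

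**Step 2: the R² difference.** From the definition of adjusted R²:

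- if 0.6 is the adjusted value, difference = P(1 − R²)/(n − 1);
- if 0.6 is the apparent value, difference = P(1 − R²)/(n − P − 1).

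| Participants analysed | 0.6 as adjusted | 0.6 as apparent |
|---|---|---|
| 249 | 15 × 0.4/248 = 0.0242 | 15 × 0.4/233 = 0.0258 |
| 332 | 15 × 0.4/331 = 0.0181 | 15 × 0.4/316 = 0.0190 |

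The bound of 0.02 is met at 332 and missed at 249 on either reading.

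**Step 3: how much loss the bound tolerates.** A difference of 0.02 needs 1 + 15 × 0.4/0.02 = 301 analysed (adjusted reading) or 16 + 15 × 0.4/0.02 = 316 (apparent reading). From 332 recruits, that allows a loss of 1 − 301/332 = 9.3% or 1 − 316/332 = 4.8%, against the 25% planned.

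**Step 4: direction with R².** At n = 249 and an adjusted R² of 0.5, the difference is 15 × 0.5/248 = 0.030. A lower R² makes the difference larger, so 0.6 is not a conservative choice for this criterion.

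**Step 5: the shrinkage claim.** S = 1 + (P − 2)/(n ln(1 − R²app)).

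- Adjusted reading at n = 249: R²app = (0.6 × 233 + 15)/248 = 0.624, so S = 1 + 13/(249 × ln 0.376) = 0.947.
- Apparent reading: S = 1 + 13/(249 × ln 0.4) = 0.943.

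Both exceed 0.9, so this claim is true at 249.

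**Step 6: the abstract's figure.** The abstract says "The planned sample size is 334 participants". Then 334 × 0.75 = 250.5, and at 250 analysed the difference is 15 × 0.4/249 = 0.0241. The result is the same.

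**The case against.** The strongest reply is that the sentence follows the recruitment figure, and at 332 it is arithmetically correct. Nowhere does the article say that 249 analysed gives a difference of at most 0.02. This stands as a matter of wording, and it is why the claim should not be called false without qualification. It does not rescue the claim for the design as planned: the 332 exists to absorb the loss, and the plan's own allowance leaves 249 with an outcome.

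A second reply is that the check is supplementary and the slip is small. That also stands. The criterion that fixes the sample size is the precision of the residual SD, and nothing in the document makes recruitment, the number of predictors or the analysis depend on 0.02. At two decimals 0.0242 would even round to 0.02, although it does not satisfy an inequality that the text says is guaranteed, and on the apparent reading 0.0258 rounds to 0.03.

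A reader might go further in three ways, none of which the document supports.

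- *That the study is too small.* The 249 and 332 do not rest on this criterion and both reproduce.
- *That overfitting is uncontrolled or that reported performance will be too optimistic.* Expected shrinkage near 0.95 argues against the first. The second depends on what is reported: giving the adjusted R² removes this difference, and the statistical analysis section leaves the modelling steps to a separate analysis plan.
- *That candidate predictors should be removed to keep the bound.* That would change the model to protect a figure that drives no design choice.

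**Conclusion.** The point holds as a minor correction. With 15 predictor parameters and R² of 0.6, the 249 participants expected after the planned loss give a difference between apparent and adjusted R² of 0.024 to 0.026, so the stated maximum of 0.02 is exceeded by about 0.004 to 0.006. It would be met only with a loss of at most about 9% (adjusted reading) or 5% (apparent reading). The wording that presents 0.6 as a demanding case points the wrong way, because the difference widens as R² falls.

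The conclusion assumes a linear model, one parameter per predictor, and that participants lost to follow-up contribute no outcome. It does not depend on which R² the 0.6 denotes. The analysable number, the recruitment target and the shrinkage claim are unaffected.

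**What to change.** Restate the sentence for the analysed number, for example: *With 249 participants analysed, 15 predictor parameters and an R² of 0.6, the expected shrinkage factor is about 0.95 and the difference between apparent and adjusted R² is about 0.024 to 0.026.* If the authors say whether 0.6 is the adjusted or the apparent value, the range reduces to a single figure: 0.024 with shrinkage 0.947, or 0.026 with shrinkage 0.943. Drop the word 'even' before the R² value.

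The cost is one edited sentence and a slightly less favourable figure. Recruitment, the number of predictors and the analysis do not change.

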#### Substudy 1: in-person MSK assessment

A recent review identified that previous ICU follow-up studies, that have included a physical assessment of some aspect of MSK health, have varied in sample size from 11 to 127 (ref). A previous UK-based single-centre prospective cohort study(ref) involving similar physical assessments had a sample size of 61 participants at six months following hospital discharge with an 18-month recruitment period. As the aim of this part of the study is to describe the specific MSK conditions and their prevalence, across three sites the target sample size is 115 participants.

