## Methods and analysis

### Aim and objectives

The aim of the MSK-ICU study is to determine and characterise the MSK health state of ICU survivors six months following admission to ICU.

Specifically, the study intends to:

Quantify the MSK health state using the MSK Health Questionnaire (MSK-HQ) and assess its relationship with QoL, employment, anxiety and depression and symptoms of post-traumatic stress disorder.Identify prognostic factors for a lower MSK-HQ Score after critical illness.Characterise the specific MSK complications experienced by patients using a standardised comprehensive MSK assessment.Evaluate patient mobility and upper limb function, and the extent of the relationship to muscle structure and function in those patients with poor MSK health state.

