#### Substudy 1: in-person MSK assessment

Participants in the primary study who self-report any MSK problem will be invited to participate in substudy 1.

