#### Substudy 2: in-person functional assessment

Participants in the primary study who report a severe MSK problem, as defined by an MSK-HQ Score of 35 or less, will be invited to participate in substudy 2.

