### Consent

Patients will only be approached for consent if the clinical and research team deem that the patient has capacity to consent. Consultee consent will not be sought from patient’s next of kin. Written versions of the participant information sheet and informed consent will be presented to the patients, who will be given time to ask questions and consider the information. Written informed consent will then be obtained by means of participant-dated signature and dated signature of the researcher who presented and obtained the informed consent. Participants will be approached prior to leaving hospital.

Participants who are eligible for either substudy will be invited to participate in one of these at the telephone follow-up. Verbal versions of the relevant participant information will be presented to the participants. If the participant provisionally agrees to participate, a written version of the participant information will be posted or emailed to them. They will then be booked an appointment to attend an in-person assessment, and asked to contact the research team to cancel that appointment if they no longer wish to participate or wish to have more time to consider the information. The participant will have at least 48 hours between telephone follow-up and the in-person assessment appointment. At the assessment appointment, written informed consent will be confirmed and recorded.

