#### Substudy 1: in-person MSK assessment

Descriptive statistics will be used to examine the individual aspects of the MSK assessment (FABQ, ROM, VAS, MRCSS, dynamometry). Correlation statistics will be used to explore the relationships between the individual aspects of assessment and the MSK-HQ Score.

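### Substudy 1 can describe MSK conditions among assessed self-reporters, but its proportions are not prevalence in ICU survivors, and the direction of the difference is uncertain

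*Protocol article*

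**What the plan says.** All references are to the protocol article.

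- Sample size, Substudy 1: the target of 115 is introduced with "As the aim of this part of the study is to describe the specific MSK conditions and their prevalence". No denominator is named.
- Aim and objectives: the study is to "determine and characterise the MSK health state of ICU survivors six months following admission to ICU". The objective that matches substudy 1 is more modest: "Characterise the specific MSK complications experienced by patients using a standardised comprehensive MSK assessment".
- Participant selection, Substudy 1: "Participants in the primary study who self-report any MSK problem will be invited to participate in substudy 1".
- Participant selection, Substudy 2: people with a severe problem, "as defined by an MSK-HQ Score of 35 or less, will be invited to participate in substudy 2".
- Consent: "Participants who are eligible for either substudy will be invited to participate in one of these at the telephone follow-up". Attendance is voluntary.
- Study procedures, Substudy 2: participants answer questions on their physical health "before undergoing the same MSK assessment as substudy 1".
- Statistical analysis, Substudy 1: "Descriptive statistics will be used to examine the individual aspects of the MSK assessment (FABQ, ROM, VAS, MRCSS, dynamometry"), followed by correlations with the MSK-HQ.

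**The concern.** Three filters stand between the ICU survivors named in the aim and the people examined in substudy 1: a reported problem, willingness to attend, and not being taken into substudy 2. Survivors who report no problem are never examined. A proportion computed on those assessed therefore describes the mix of conditions among attenders with a problem, not how common the conditions are in survivors.

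The word prevalence invites the second meaning. The Introduction uses it for MSK conditions in ICU survivors, and the sample size paragraph sets substudy 1 beside earlier ICU follow-up cohorts. The study is meant to inform targeted rehabilitation. A figure on a base of 115 labelled as prevalence could be carried into service planning or later trial design as a rate in survivors.

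**Working it through.** **1. The plan's own figures.** The 115 comes with no formula, precision target or expected prevalence. It is set by reference to earlier studies (11 to 127 participants, and one of 61), so there is nothing to reproduce. The primary-study figures do reproduce:

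- With 15 predictors, residual df = n − 15 − 1. The margin √max(χ²₀.₉₇₅/df, df/χ²₀.₀₂₅) is 1.1001 at n = 248 and 1.0998 at n = 249.
- 249 / (1 − 0.25) = 332.

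I therefore take 249 as the planned number of telephone respondents. At n = 115 the 95% half-width, 1.96 × √(p(1 − p)/115), is 7.3 points at p = 20%, 8.4 at 30% and 9.1 at 50%.

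**2. Who is examined.** If nobody enters both substudies, 115 + 35 = 150 people have the MSK assessment. That is 150/249 = 60% of respondents, and 115/249 = 46% for substudy 1 alone.

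**3. Selection on self-report.** Let s be the share of respondents reporting a problem, c the prevalence of a given condition in reporters and c₀ that in non-reporters. Prevalence in respondents is P = s·c + (1 − s)·c₀. The documents give none of these, so all are assumed. With representative attenders, substudy 1 shows c. For c = 30%:

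| s | P if c₀ = 0 | c/P | P if c₀ = 10% | c/P |
|---|---|---|---|---|
| 0.4 | 12% | 2.50 | 18% | 1.67 |
| 0.6 | 18% | 1.67 | 22% | 1.36 |
| 0.9 | 27% | 1.11 | 28% | 1.07 |

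If c₀ = c the ratio is 1.0. Filling both substudies with different people needs 150 reporters, so s of at least 0.60 with 249 respondents, or 150/332 = 0.45 with no loss at all. The row for 0.4 therefore applies only if a target is missed.

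**4. Diversion of severe cases.** Suppose 35 severe reporters go to substudy 2, substudy 1 represents the other reporters, and c₀ = 0. Write c_s for prevalence in the diverted group and c_m for that in the rest.

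- s = 0.6: reporters 0.6 × 249 = 149.4, remainder 114.4. P = (35·c_s + 114.4·c_m)/249 = 0.141·c_s + 0.459·c_m. Substudy 1 shows c_m, which is below P when c_m < (0.141/0.541)·c_s, about 0.26·c_s.
- s = 0.9: reporters 224.1, remainder 189.1. P = 0.141·c_s + 0.759·c_m, and substudy 1 is below P when c_m < 0.58·c_s.

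An illustration with larger diversion: s = 0.8, half of reporters severe, c_s = 60%, c_m = 20%, all severe cases diverted, c₀ = 0. Reporters overall: 0.5 × 60% + 0.5 × 20% = 40%. Respondents: 0.8 × 40% = 32%. Substudy 1 shows 20%.

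**5. Attendance.** Nothing in the article indicates whether attenders have more or fewer conditions than reporters who decline.

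**6. Dividing by everyone telephoned.** Cases found over all respondents err the other way. With c = 30%, 0.30 × 115 = 34.5 cases, and 34.5/249 = 13.9%, against 18% at s = 0.6 and c₀ = 0. Non-attenders are counted as unaffected, and so are any impaired non-reporters.

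**The case against.** The sample size sentence does not say prevalence in ICU survivors; that population is carried over from the study aim. Prevalence among people with a reported problem is a possible reading, since the entry condition is stated openly and the listed objective says only characterise. The article calls the substudies exploratory, and it nowhere says that a figure over 115 will be presented as a rate in survivors. Denominators and weighting are commonly left to a full protocol or SAP that is not shown here.

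Much of this stands. Silence on weighting or intervals is not a fault in a condensed article, and I do not count it as one. But prevalence is stated as an aim, and eligibility is fixed in the same document. No later analysis can recover findings in people who were never examined. The SAP promised under Statistical analysis is described for model development, which is the primary-study regression. At best the term is ambiguous.

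A reader might also infer that substudy 1 will overstate prevalence in survivors. The documents do not support that as a certainty. Substudy 2 can draw off people with the worst MSK-HQ scores, and this can reverse the direction, as step 4 shows. Setting c₀ = 0 also gives the largest upward gap for given s and c; any impairment in non-reporters narrows it.

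**Conclusion.** The concern holds in this form: as designed, substudy 1 yields proportions conditional on self-report, attendance and allocation, and these are not prevalence in ICU survivors. Selection on self-report probably pushes them up, diversion of severe cases pushes them down, the effect of non-attendance is unknown, and the net direction is not certain.

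The size cannot be fixed from the documents. Under the assumed inputs the ratio runs from 2.5 down to 1.0 without diversion, and falls below 1 in the diversion illustration (20% against 32%). At c = 30%, s = 0.6 and c₀ of 0 or 10%, the gap of 12 or 8 points is about as large as the 8.4-point half-width, and a confidence interval would not show it. These figures are illustrations, not forecasts.

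The primary regression is untouched. The point concerns labelling and a modest change of analysis, and it is worth correcting before results are reported.

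**What to change.** 1. In the sample size text for substudy 1, replace prevalence with: distribution among assessed participants with a self-reported MSK problem. Use the same label in the substudy 1 analysis. Report beside it the proportion of telephone respondents who report a problem and the proportion of those who were assessed.
2. Pool the identical MSK assessments from substudy 2, allowing for the different chance of assessment by severity. A simple way is to estimate each condition separately for MSK-HQ 35 or less and above 35, then combine the two using their shares among all self-reporters in the telephone data. In the illustration of step 4 this gives 40% among reporters, where substudy 1 alone shows 20%.
3. If a survivor-level figure is wanted, compute it over telephone respondents at sites that offer in-person assessment, counting non-reporters as having no reported condition. The site restriction matters because the sample size text for substudy 1 refers to three sites while Study settings places the substudies in four trusts. A site that assesses nobody cannot be represented by weighting. Label the figure a lower bound for symptomatic conditions, resting on the assumption that assessed self-reporters represent the rest.
4. Inverse-probability weighting on data held for all respondents is optional, as a sensitivity analysis.

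The cost is a change of wording and a short calculation on data already collected. The price is somewhat wider intervals and a more modest claim.
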